#### Patient Recruitment and Data Collection

All suitable patients with abdominal pain will be identified on ED presentation and approached by a research nurse (if available) or the treating clinician for consent for (1) study participation, data access, and collection and (2) follow-up contact. Patients who are not captured on the index visit (ie, “missed” recruitment) will be identified by the research team through a review of the daily ED attendance record using the terms “abdominal pain,” “appendix” or “appendicitis” on triage text or discharge diagnosis text “appendicitis” or “abdominal pain.”

Basic demographic data of missed patients (including any interventions performed and management) will be recorded on a separate datasheet and collected at the earliest possible time. Missed cases, if assessed by the research team to be eligible, will have a retrospective case report form completed by the treating clinician, if possible, and the family will be contacted via phone or text message to obtain informed verbal consent for inclusion retrospectively for (1) study participation and data access and collection and (2) follow-up contact. Follow-up will not be conducted for patients who are admitted to the hospital under an inpatient medical or surgical team or those who experience severe morbidity, such as a new diagnosis of chronic illness or permanent disability, or are deceased. Participants who decline consent for data access and collection will be excluded from the study.

The treating clinician will complete, at the time of the ED visit, or retrospectively if missed initially, a case report form recording:

demographic data (sex and age),eligibility (inclusion and exclusion criteria),caregiver verbal consent,the clinician's seniority and their perceived likelihood of appendicitis on a Visual Analog Scale from 0 being “Extremely unlikely” to 10 being “Extremely likely” and whether this perceived likelihood was formed before or after investigations (bloods, imaging, or both),history of the presenting complaint (location of initial pain, duration of pain, highest pain score, highest reported temperature during this illness, right lower quadrant (RLQ) or right iliac fossa (RIF) pain on arrival to ED, pain migration to RLQ or RIF, progression of pain, gradual onset of pain, pain pattern, history of pain with walking, anorexia, nausea, vomiting, difficulty with micturition, pothole tenderness, family history of appendicitis, respiratory tract infection in last 2 weeks, and bowel habit), andexamination findings (RLQ tenderness, RIF tenderness, tenderness worst in RLQ, tenderness outside RLQ, presence of hop, cough, or percussion tenderness, degree of rebound tenderness, abdominal guarding, Rovsing sign, nature of bowel sounds, palpable abdominal mass, and abdominal rigidity).

Clinician management will proceed independently of study participation.

All data collected at sites will be transcribed to a REDCap (Research Electronic Data Capture; Vanderbilt University) database [66]. The following additional data will be collected from the patient's medical records: blood test results (white cell count, absolute neutrophil count, neutrophilia, and C-reactive protein), urinalysis (presence of leukocytes or nitrites), which will then allow the various CPSs to be automatically calculated in REDCap.

Between 30-60 days after the ED visit, the site research team will collect the following parameters in all eligible patients through a medical record review:

detailed demographics (postcode, Medicare status, race or nationality, and referral source),prehospital management,management and imaging were undertaken both pre-ED in the community and the study hospital,time-related data (times of triage, clinician evaluation, ED, and hospital discharge),duration of ED and hospital stay,admission status and specialty unit consultations, including intensive care admission,medication use in ED, including antibiotics and analgesia,related surgical and nonsurgical interventions,other significant pathology or adverse events, including mortality, anddisposition.

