**Figure 1 figure1:**
[figure not shown]
Study process and timeline. CRF: case report form. *Dependent on consent and need for follow up. **Contact for retrospective consent can be performed concurrently with follow up in 30-60 days.

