### Comparison With Previous Work

The inclusion of 30 CPSs and the prospective nature of the study, with a planned study size of 2400 patients would make it one of the largest prospective validation studies in children, comparing the largest number of CPSs compared with previous studies [36,39,40,43,44,59,60]. A total of 10 EDs across ANZ will contribute data, including a mix of community and tertiary pediatric centers, which will allow the study's findings to be broadly generalizable across ANZ EDs compared to previous ANZ studies in single centers [6,43,44].

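### Forms for missed children may be completed retrospectively, with no time limit or blinding to results, and the ranking of CPSs by AUC does not separate them

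*Protocol article*

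**What the plan says.** Under Patient Recruitment and Data Collection, children not captured at the visit are "identified by the research team through a review of the daily ED attendance record using the terms" that follow. These are triage terms and also "discharge diagnosis text “appendicitis” or “abdominal pain". Those judged eligible "will have a retrospective case report form completed by the treating clinician, if possible", and the family is approached for "informed verbal consent for inclusion retrospectively".

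The same form serves both routes. It is completed "at the time of the ED visit, or retrospectively if missed initially, a case report form recording" demographics, history, examination findings and the gestalt visual analog scale. Blood and urine results are taken separately from the medical record. The only timing item on the form concerns gestalt: "whether this perceived likelihood was formed before or after investigations (bloods, imaging, or both".

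The Follow-Up section gives one safeguard against information bias: the research team, not the clinician, calculates the scores. Statistics and Interim Analysis identifies the best CPS by the highest AUC and mentions no split by form timing. Strengths and Limitations does not mention retrospective forms, and Comparison With Previous Work relies on "the prospective nature of the study".

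**The concern.** Many of the inputs are matters of judgement or recall: pain migration, anorexia, rebound, guarding, Rovsing sign and, above all, gestalt. A clinician completing the form after the visit may already know the scan, operation or histology result. Having the research team calculate the scores protects the arithmetic, not the recorded inputs.

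Two results are exposed. The first is the ranking of the 30 CPSs: laboratory items are immune to hindsight and clinical items are not, so scores that lean on symptoms and signs could move relative to the others. Selection by highest AUC has no margin, so a small differential shift could change which CPS comes first. The second is the comparison with gestalt (secondary aim 1A in Objectives), which is defined as the likelihood judged during ED assessment. A gestalt value entered once the diagnosis is known does not measure that.

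**Working it through.** **1. The plan's own figures.** Inputs from Sample Size and Power Calculation: N = 2400, appendicitis rate 30%, all CPSs calculable in half.

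- Cases: 2400 × 0.30 × 0.50 = 360. Non-cases: 2400 × 0.70 × 0.50 = 840.
- Hanley-McNeil: SE² = [A(1−A) + (n₁−1)(Q₁−A²) + (n₀−1)(Q₂−A²)] / (n₁n₀), with Q₁ = A/(2−A) and Q₂ = 2A²/(1+A).
- A = 0.95: SE 0.0082, half-width 1.96 × SE = 0.016. A = 0.75: SE 0.0164, half-width 0.032. Both match the plan.
- Power for paired AUCs: Φ(Δ/√(SE₁² + SE₂² − 2r·SE₁·SE₂) − 1.96). The plan gives a score correlation of 0.5, not the correlation r between AUCs, so r = 0.40 to 0.50 is assumed. Power is 0.89 to 0.94 for 0.80 v 0.85 and 0.94 to 0.97 for 0.90 v 0.94. The stated >85% and >90% hold.

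The sample-size arithmetic is sound. It covers sampling error, not this bias.

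**2. Illustration of hindsight (all inputs assumed).** Binormal scores with unit SD and μ = √2·z(A). A share f of forms is retrospective; in those, cases move up and non-cases down by d SD. Then

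pooled AUC = (1−f)²Φ(μ/√2) + 2f(1−f)Φ((μ+d)/√2) + f²Φ((μ+2d)/√2).

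Example, A = 0.80, f = 0.20, d = 0.2: 0.64 × 0.800 + 0.32 × 0.837 + 0.04 × 0.870 = 0.815, a rise of 0.015.

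Rise in pooled AUC at true AUC 0.80:

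| d | f = 10% | 20% | 30% | 50% |
|---|---|---|---|---|
| 0.1 | 0.004 | 0.008 | 0.011 | 0.019 |
| 0.2 | 0.007 | 0.015 | 0.022 | 0.036 |
| 0.3 | 0.011 | 0.021 | 0.031 | 0.051 |

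**3. Opposite direction.** If retrospective forms carry only random recall error (extra variance 0.25 to 1.0), the same model lowers an AUC of 0.80 by 0.003 to 0.042 over f = 10% to 50%.

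**4. What reaches the ranking.** Inflation common to two scores measured in the same children largely cancels; the difference in inflation remains. At f = 20% and equal true AUCs of 0.80, a score with d = 0.2 against one with d = 0.1 shows a false gap of 0.0147 − 0.0076 = 0.007. Against a score with no exposure the gap is the full 0.015. The latter is an outer case, since the Introduction says most CPSs combine clinical and laboratory items.

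**5. Cost of dropping retrospective forms** (N held at 2400, 0.80 v 0.85, r = 0.45):

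| f | Cases | Half-width at AUC 0.75 | Power |
|---|---|---|---|
| 10% | 324 | 0.034 | 88% |
| 20% | 288 | 0.036 | 84% |
| 30% | 252 | 0.038 | 79% |
| 50% | 180 | 0.045 | 65% |

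The stated >85% power would be lost somewhere between a 10% and a 20% share.

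**The case against.** The attendance record is reviewed daily, so most missed children may be found quickly. The search also uses triage text and abdominal pain, so it is not aimed only at cases, and an ED discharge diagnosis is not the histology reference standard. The form does ask whether gestalt came before or after investigations. A condensed article may leave a sensitivity analysis to a fuller plan that is not shown.

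Much of this stands as mitigation, but it does not remove the point. No limit on delay is fixed. The gestalt item does not record whether the final diagnosis was known, and on a retrospective form its answer is itself recalled. A later analysis plan cannot undo unblinded recording, and it can separate the forms only if their timing was captured.

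A reader might infer more than the text supports:

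- That forms are filled in from memory. The protocol does not say so, and use of the ED notes is not excluded.
- That forms may be completed at 30-60 days. The Figure 1 caption, "Contact for retrospective consent can be performed concurrently with follow up in 30-60 days", concerns consent contact only.
- That the AUCs are inflated. The net direction is unknown.
- That inflation of a single AUC can be set directly against the 0.05 target. That target is a difference between two AUCs, so only differential bias counts.
- That the primary set should be limited to forms completed before imaging. That would also drop children enrolled prospectively after external investigations, could add selection bias and would cost power.

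**Conclusion.** The concern holds as a possible bias of unknown size. As written, the plan allows unblinded retrospective recording of subjective predictors and gestalt, with no time limit, and ranks the CPSs without separating those forms. Hindsight would probably push AUCs up and random recall error would push them down. Because laboratory items are protected, the effect can differ between CPSs and so affect their order.

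On the assumed model the rise in one AUC is 0.004 to 0.051. Only the upper part of that range is comparable with the planned half-widths of 0.016 to 0.032. Every figure in that range rests on an assumed retrospective share and shift, since the document gives neither share nor delay. The documents do not support a claim that the results are inflated, nor that the primary CPS analysis must exclude these children. The gestalt comparison, a secondary aim, is the most exposed, because a retrospective value departs from its own definition.

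**What to change.** 1. Flag each form in REDCap as index-visit or retrospective, with its completion date. For forms still to be completed, also record whether imaging, operative or histology results were known to the clinician.
2. Leave retrospective forms out of the gestalt AUC and the CPS-versus-gestalt comparison.
3. Keep retrospective forms in the main CPS analysis, and prespecify a sensitivity analysis giving the CPS AUCs and ranking with and without them. Call a best-performing CPS robust only if it leads in both.
4. Report the retrospective share and the delay, and list the issue as a limitation.

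Cost: fewer children in the gestalt comparison and a little more analysis. The set without retrospective forms is smaller, so a change of leader there may be chance and should be read with its confidence intervals. The Results section reports 1227 of 2400 children (51%) already enrolled and followed up, so the results-known item cannot be collected prospectively for them. Missed children are already kept on a separate datasheet, which should allow the basic flag to be set.

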#### Follow-Up

All eligible patients will be contacted for a follow-up survey except when (1) the parent or guardian declined follow-up on the initial presentation, (2) the participants were admitted under an inpatient medical or surgical team with no further representations to ED within the follow-up period of 30 days, or (3) participant identified by the site research team to have experienced clinically significant adverse events. Any approved parental contact will occur via a telephone call, email, or text, with scripts for each contact method provided to participating sites. Follow-up emails will be automatically generated and sent out twice during the follow-up period with identifiable data accessible only to the local study site and the central coordinating study team, and will be removed from the REDCap database at 61 days postenrollment date by the local study research team. A maximum of 3 contact attempts will be made. If more than 60 days have elapsed from the time of presentation, or if there have been three failed contact attempts, the patient follow-up will be regarded as unsuccessful. The medical record for patients unable to be contacted will be reviewed and if sufficient information is documented in the medical record, this information may be used to substitute for the failed contact.

The follow-up survey will determine the following:

if the child had any problems with abdominal pain since being discharged from the ED,if the child missed any childcare or school because of abdominal pain,if the carers took any time off work because of the child’s ongoing pain, andif the child has been seen by another doctor, health professional, or hospital since the visit to the ED.

It will also collect the following details: details of ongoing problems; the number of missed days of school or childcare; the number of days off work; types and numbers of medical reviews; additional medical diagnoses; need for and duration of ED stay and hospital admissions including investigations (with a review of the relevant medical record); and related surgical interventions. Any eligible participants whose parent or guardian consented for data access and collection but declined follow-up will have their data collected and analyzed, but will not be contacted for follow-up. If participants withdraw consent and discontinue participation in the study at any time, there will be no effect on their medical care or access to treatment. If a participant withdraws before completing the study follow-up period, any known reason for withdrawal will be documented in the database. All information already collected as part of the study will be retained for analysis, but no further efforts will be made to follow up or obtain additional information regarding the participant. As an observational study, there are no anticipated adverse events related to the research. During the follow-up contacts, if any medical issues are identified by research staff, they will be referred to the managing clinicians (for patients in hospital), or the site investigator (for questions during follow-up), who will refer, if required, the patient to their general practitioner or ED for review.

To minimize information bias, the calculation of the CPSs will be performed by the research team and not by the treating clinician. If the study participant is transferred from a nonstudy site to a study site, the data collection form will be completed by the initial treating physician at the study site; if the study participant is transferred from a study site to a second study site, this will ideally be completed by the initial treating physician at the first study site.

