### Outcome Measures

#### Overview

The primary outcome is the presence of appendicitis; this will be confirmed through the histopathology report when available, or the operation report if not available. Patients diagnosed with appendicitis but managed nonoperatively will be followed up to confirm the presence of appendicitis in cases where interval appendectomy was performed or excluded from analysis in cases treated conservatively with antibiotics only. A nonappendicitis diagnosis will be confirmed on follow-up via either recording of the primary diagnosis on hospital discharge if admitted to hospital, or contact at 30-60 days to ensure no progression in symptoms or representation to hospital for those discharged directly from the ED. The area under the receiver operating characteristic (ROC) curve (AUC) will be calculated for the various published CPS for the primary outcome of appendicitis.

Secondary outcomes include rates of uncomplicated and complicated appendicitis (defined as the presence of perforation, extraluminal fecalith, diffuse intraperitoneal pus, or a well-formed abscess) [62], negative appendectomy cases (based on histopathological findings), and missed appendicitis cases. These will be confirmed through the histopathology report when available, and the operation report if not available. To identify missed appendicitis cases, families of children who did not undergo appendectomy and were discharged directly from the ED will be contacted within 30-60 days of hospital discharge to assess for postdischarge status and whether their child had an appendectomy in the interim. For families unable to be contacted, medical records will be reviewed at 60 days to assess for representation. Other secondary outcome measures include length of hospitalization, rates of investigations, and rates of interventions.

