### Strengths and Limitations

Our study will allow the simultaneous comparative application and validation of 30 CPSs for diagnosing pediatric appendicitis outside their derivation settings. In addition to a high recruitment rate, the study will depend on high follow-up rates to ensure that our results accurately represent the whole population of children presenting to the ED with suspected appendicitis, as all patients lost to follow-up will be excluded from data analysis for CPS calculation. Ideally, all patients with abdominal pain would undergo investigations or appendectomy to determine the presence or absence of appendicitis; however, this would increase the rate of unnecessary investigations and potentially the rate of negative appendectomies should investigations be inconclusive. Therefore, a similar methodology to a previous PREDICT study looking at clinical decision rules for head injuries [72] was adapted using follow-up telephone or email contact to establish the presence or absence of appendicitis after discharge from the ED. It is also possible some patients with appendicitis would be treated conservatively with antibiotics and excluded from the study; however, this would represent a small number of patients as this is an uncommon practice in ANZ with only one patient in the feasibility study treated conservatively after a radiological diagnosis of appendicitis due to parental preference [43].

The predictor variables for the 30 CPSs were derived solely from original publications [2-31] and amalgamated into a single case report form developed by the study authors, which may introduce an element of interpretation in terms of the exact clinical terminology used in ANZ ED settings. The difficulty and variability of prospective clinician data collection in busy EDs in completing the case report form may result in a significant proportion of patients with multiple missing variables to calculate all CPSs; however, the feasibility study demonstrated the viability of the case report form used with all study CPSs being calculable in the majority of the patient cohort (ranging from 52% to 93.3%) based on constituent variables available [43]. Implementation of an appropriate method, such as multiple imputation, will be considered to minimize potential biases that may arise from missing data in the multicenter study [73].

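### The information-bias safeguard keeps the scores from the treating clinician only; for ED-discharged children without contact, an undefined record-sufficiency judgement not stated to be masked to the scores decides inclusion as a non-case

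*Protocol article*

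**What the plan says.** All statements are in the protocol article.

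- **Safeguard (Follow-Up):** with the stated aim of limiting information bias, "the calculation of the CPSs will be performed by the research team and not by the treating clinician".
- **Where the scores arise (Patient Recruitment and Data Collection):** site data are transcribed to REDCap and blood and urine results are added, "which will then allow the various CPSs to be automatically calculated in REDCap".
- **Who reviews the record (same section):** between 30 and 60 days, "the site research team will collect the following parameters in all eligible patients through a medical record review". The list includes interventions, other significant pathology and disposition.
- **Reference standard (Outcome Measures, Overview):** for appendicitis, "this will be confirmed through the histopathology report when available, or the operation report if not available". For its absence, "recording of the primary diagnosis on hospital discharge if admitted to hospital, or contact at 30-60 days to ensure no progression in symptoms" or re-presentation, the contact route being for children discharged directly from the ED.
- **When contact fails, according to Outcome Measures, Overview:** records are checked at 60 days for re-presentation.
- **When contact fails, according to Follow-Up:** the record is reviewed and "if sufficient information is documented in the medical record, this information may be used to substitute for the failed contact".
- **Consequence of loss (Strengths and Limitations):** the results depend on high follow-up, "as all patients lost to follow-up will be excluded from data analysis for CPS calculation".

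**The concern.** In a diagnostic accuracy study the index test should not influence the reference standard or the decision on who is analysed. The stated safeguard deals with one side of this, since the clinician does not calculate the scores. It does not deal with the other side. The scores sit in the study database, a site research team reviews the record afterwards, and nothing stated keeps the two apart.

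That would matter little if every outcome were fixed by an outside source. For uncontacted ED-discharged children it is not. Whether such a child counts as a non-case or is dropped turns on a sufficiency test that has no criterion and is permissive in wording. A thin record could be accepted more readily for a low-scoring child than for a high-scoring one. High-scoring non-cases would then be under-represented and the scores would look more accurate than they are. The Statistics section names the best score by the highest AUC, without a margin, among 30 scores, so even a small artefact is unwelcome. Unlike sampling error, it does not shrink as recruitment continues.

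**Working it through.** **1. The plan's own figures.** Cases with all scores calculable: 2400 × 0.5 × 0.30 = 360, which leaves 840 non-cases. The Hanley-McNeil variance is [A(1−A) + (m−1)(Q₁−A²) + (n−1)(Q₂−A²)]/(mn), with Q₁ = A/(2−A), Q₂ = 2A²/(1+A), m = 360, n = 840.

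- A = 0.95: (0.0475 + 359 × 0.00226 + 839 × 0.02314)/302400 = 6.70 × 10⁻⁵. Half-width 1.96 × 0.00819 = 0.016, as stated.
- A = 0.75: (0.1875 + 359 × 0.0375 + 839 × 0.08036)/302400 = 2.68 × 10⁻⁴. Half-width 1.96 × 0.01637 = 0.032, as stated.

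The same formula gives 0.030 at A = 0.80 and 0.022 at A = 0.90. No stated figure is disputed; these serve as a yardstick.

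**2. Who is exposed.**

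| Group | Outcome settled by | Room for judgement |
|---|---|---|
| Operated | Histopathology, else operation report | Little |
| Admitted, not appendicitis | Discharge diagnosis | Little |
| ED-discharged, contacted | Contact, with scripts supplied to sites | Little |
| ED-discharged, not contacted | 60-day re-presentation check, or record if judged sufficient, else excluded | Yes |

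In the last row the three statements do not fit together. A child with no contact and no re-presentation could be a non-case under Outcome Measures, a matter of judgement under Follow-Up, and excluded under Strengths and Limitations. Families who declined follow-up add to this row: Follow-Up says their data are analysed without contact.

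**3. Effect on specificity.** The document gives no unreachable share and no specificity. Assumed: true specificity 80%; 15% of non-cases unreachable (range 5-25%); false positives equally common among them.

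- Non-cases 2400 × 0.70 = 1680; false positives 1680 × 0.20 = 336.
- Unreachable 1680 × 0.15 = 252; false positives among them 252 × 0.20 = 50.4.
- Half of these dropped: 1 − (336 − 25.2)/(1680 − 25.2) = 1 − 310.8/1654.8 = 81.2%.
- All dropped: 1 − (336 − 50.4)/(1680 − 50.4) = 1 − 285.6/1629.6 = 82.5%.
- All dropped, 5% unreachable: 1 − 319.2/1663.2 = 80.8%. At 25%: 1 − 252/1596 = 84.2%.

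PPV = TP/(TP + FP) rises because FP falls. NPV = TN/(TN + FN) contains no false positives and does not change.

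**4. Effect on AUC.** Assumed: equal-variance binormal score, and a fraction u of non-cases uncontacted. As an extreme, records are accepted only for those scoring below the non-case median. Then a fraction u/2 of all non-cases is lost from the upper half, and

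shift = (u/2)(A − A_up)/(1 − u/2),

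where A_up is the AUC against upper-half non-cases only. Numerical integration gives A_up = 0.640, 0.7225 and 0.810 for A = 0.80, 0.85 and 0.90. Example: A = 0.80, u = 0.20 gives 0.10 × 0.16/0.90 = 0.018.

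| True AUC | u = 5% | u = 10% | u = 20% |
|---|---|---|---|
| 0.80 | 0.004 | 0.008 | 0.018 |
| 0.85 | 0.003 | 0.007 | 0.014 |
| 0.90 | 0.002 | 0.005 | 0.010 |

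All are below the half-widths at these AUCs (0.022 to 0.030) and below the differences of 0.04 and 0.05 used for power.

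**The case against.** A reader might infer that the research team assigns the outcome with the scores in view. The documents do not support that. REDCap computes the scores, so staff have no discretion over their values. Operated, admitted and contacted children are settled by reports, discharge diagnoses or scripted contact. The sentence on substituting the record is in the passive and names no decider. The article speaks of the research team, the site research team and a central coordinating team, and does not say that they are the same people. Nowhere does it say that record reviewers see the calculated fields. That is inferred from the absence of a stated separation, and a condensed article may leave user rights to the full protocol.

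Two further inferences also fail. NPV is not inflated by dropping false positives. It could be inflated only if missed cases with low scores were accepted as non-cases, which is a different route and not quantified here. Nor is there ground for saying that pARC would gain most: the article states a hypothesis about pARC, not that staff look at it.

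The magnitude is assumed, and probably generous. The unreachable share is applied to all non-cases, although admitted ones need no contact, and higher-risk children may more often be admitted. Selection on general risk would also move correlated scores together, so the ranking would change less than any single AUC.

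All of this narrows the point. What remains is that the sufficiency test is undefined, decides inclusion, does not fit the other two statements and is not stated to be made without the scores.

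**Conclusion.** The concern holds in a limited form. The stated safeguard covers the treating clinician only. For ED-discharged children without successful contact, a discretionary judgement, possibly made with scores in view, decides whether they are analysed as non-cases.

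On assumed inputs the effect is small: specificity of 80% reported as 81.2% to 82.5% with 15% unreachable (80.8% to 84.2% over 5-25% if all unreachable false positives are dropped), and AUC raised by at most about 0.02 in an extreme scenario with 20% uncontacted. These sizes depend on the assumed unreachable share, specificity, score model and strength of selection, none of which is in the documents. The sample size, precision and power statements are unaffected.

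This is a cheap improvement, not a defect that undermines the study. It is worth making because the best score is chosen on the highest AUC alone. If the full protocol already masks the reviewers, saying so would settle that half of the point; the three statements on uncontacted children would still need reconciling.

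**What to change.** 1. Compute the CPS fields, or reveal them and the gestalt rating, only after the outcome form is locked. This is a change of REDCap user rights.
2. Replace the sufficiency wording in Follow-Up with one fixed rule for all uncontacted ED-discharged children, including those whose family declined follow-up. Make Outcome Measures and Strengths and Limitations agree with it.
3. Add a sensitivity analysis that repeats the AUCs with all uncontacted children handled alike.
4. For children already processed (1227 with completed follow-up at submission, of 2400 planned), compare the scores of uncontacted children whose record was accepted with those whose record was refused.

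Cost: one access setting, a short text change, one sensitivity analysis and one descriptive comparison. Sites would no longer see scores during data entry, so score-level data checks move to the central team. Masking is only partial, because a record reviewer still sees the symptoms, examination findings and blood results that make up the scores. The fixed rule therefore matters at least as much as the hidden fields.
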